#### Statement of Objectives and Hypotheses

- 1. **Objectives**

1. To examine whether a single dose of olanzapine (OLA) given to young healthy volunteers during pancreatic euglycemic clamps can inhibit the ability of a central insulin stimulus (i.e. intranasal insulin administration) to reduce endogenous glucose production (EGP).
2. In an exploratory aim, we will examine whether a single dose of OLA can inhibit improvements associated with intranasal insulin administration on specific cognitive domains (visuospatial, and verbal memory). We will also explore the effects of insulin and OLA on neurochemical and neurohemodynamic measures.

The study will have two separate and parallel arms. The first arm will test the first objective while the second arm will examine the second objective. Participation in one arm does not exclude participation from the other, provided sufficient wash out period between the 2 arms is maintained (>1 week).

**1.2 Hypotheses**

1. Primary hypothesis (Glucose metabolism: Pancreatic euglycemic clamp experiments):

Intranasal insulin (INI) will be associated with a decrease in **endogenous** **glucose production** (EGP) (our primary outcome measure) relative to intranasal placebo (INP). This effect of glucose production lowering by INI will be lost if OLA is co-administered. In the absence of INI administration, there will be no difference between OLA and oral placebo (PL). We do not expect any of the treatments to differ with respect to glucose disposal (Gd). Predicted differences between treatments in Dextrose Infusion Rate (InfR) reflect differences in EGP. In summary, we predict the following treatment effects **relative to the INP-PL group** (i.e. no active treatment) (Table 1):

| Treatments | | Measures derived from Pancreatic clamp procedure | | |
| --- | --- | --- | --- | --- |
| Intranasal | Oral | Dextrose InfR | EGP | Gd |
| INI | PL | 🡹 | 🡻 | 🡺🡸 |
| INI | OLA | 🡺🡸 | 🡺🡸 | 🡺🡸 |

1. Secondary hypothesis (Cognition):

OLA will be associated with decrements in cognitive measures as compared to PL. Further, OLA will block the beneficial effect of INI on cognition. Hence, there will be no difference between the INI and INP in the presence of OLA (and performance in both these arms will be worse than that in the INP-PL arm). In summary, we predict the following treatment effects **relative to the INP-PL group** (Table 2):

| Treatments | | Cognition:  (visuospatial memory and verbal memory) |
| --- | --- | --- |
| Intranasal | Oral |  |
| INI | PL | 🡹 |
| INP | OLA | 🡻 |
| INI | OLA | 🡻 |

- 1. We also hypothesize that INI will result in adaptive changes in neurochemical and neurohemodynamic measures as studied using MRI techniques. Furthermore, OLA will block these effects of INI.

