Power Analysis: Using data from [name] previous study also employing a randomized cross-over design^32^, we found that a sample of 16 subjects would be needed to detect a 20% difference between INI-PL relative to INP-PL in endogenous glucose production, with 80% power to detect an effect size Cohen’s d = 0.66. We used a conservative estimate of the correlation between period 1 and period 2 (= 0.2). To account for the three comparisons among the three groups in the metabolic arm (using Bonferroni adjustments for multiple tests) and based on an expected attrition rate of 20% and the need to keep the total number of participants as a multiple of 3 (to counterbalance the order effects of the four treatment periods), we will recruit 27 participants to the metabolic arm of the study. To account for the six comparisons among the four groups in the cognitive arm of the study, we will recruit 32 participants to this arm. As the cognitive portion of the study is exploratory, data will be used to generate future sample sizes. The fMRI data will be analyzed using SPM12. Contrasts will be generated for activation differences between task conditions. ASL and resting state fMRI data will be analyzed using appropriate tools available in SPM12 and FSL libraries. MRS data will be analyzed using LCModel to quantify glutamate content in the VOI. Data across modalities will be analyzed in a repeated measures ANOVA design to investigate the effect of treatments. These analyses will be conducted by SMA under the supervision of AGG and AV.

To address our primary hypothesis, which is the comparison within subject between treatments, Mixed Effect Models will be used. The four treatments, time, and sequences will be entered as predictors and subject will be used as clusters in a random intercept model. In addition to examining outcome measures within subjects across treatments, predictors accounting for order effects will be included in the analyses. Mixed Effect Models will be adjusted with SAS System 9.4. A similar approach is used for cognitive data, where measures of sedation will be used as covariates.

1. **Risks/Benefits**

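### Loss of the intranasal-insulin effect is predicted as no difference from INP-PL, with no criterion, and the direct INI-OLA versus INI-PL contrast that answers Objective 1 is not designated

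*Protocol*

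**What the plan says.** Objective 1 (Protocol, Statement of Objectives and Hypotheses) asks whether olanzapine "can inhibit the ability of a central insulin stimulus (i.e. intranasal insulin administration) to reduce endogenous glucose production (EGP". Section 1.2 then predicts that INI lowers EGP relative to INP and adds: "This effect of glucose production lowering by INI will be lost if OLA is co-administered". Table 1 sets out the predictions with INP-PL as the reference: EGP falls under INI-PL and is unchanged under INI-OLA. It has no entry for INI-OLA against INI-PL.

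The Data Analysis Plan and Power Calculation section sizes the arm on one contrast: "a sample of 16 subjects would be needed to detect a 20% difference between INI-PL relative to INP-PL in endogenous glucose production". The power there is 80%, for a standardised effect of 0.66 and a within-subject correlation of 0.2. On multiplicity it says "To account for the three comparisons among the three groups in the metabolic arm (using Bonferroni adjustments for multiple tests"; with an attrition allowance, this leads to "we will recruit 27 participants to the metabolic arm of the study". The primary analysis is a mixed model comparing treatments within subject. The three comparisons are not ranked, none is named as the test of blockade, and no margin defines loss of the effect.

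**The concern.** Objective 1 concerns a difference: is EGP higher under INI-OLA than under INI-PL? Table 1 describes a different comparison, with an expected null against INP-PL. If the conclusion were drawn from one significant and one non-significant comparison with INP-PL, the trial would be comparing significance levels and not testing olanzapine's effect on the insulin response. A non-significant INI-OLA versus INP-PL result is compatible with full, partial or no blockade.

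Bonferroni over all three pairs spends alpha on a comparison that the hypothesis itself expects to be null. By raising the bar for significance, it also makes that null easier to obtain. At stake is the trial's main conclusion, and in particular whether it can say that olanzapine abolished the effect or only that it reduced it.

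**Working it through.** **Inputs.** From the Data Analysis Plan and Power Calculation section: d = 0.66, 80% power, correlation 0.2, three Bonferroni comparisons. From the Participants section: 27 complete data sets, with dropouts replaced. Alpha, sidedness and the standardiser of d are not stated. I assume a familywise 0.05, two-sided, so 0.05/3 = 0.0167 per pair, and carry two readings of d:
- d already on the SD of the within-subject difference: dz = 0.66.
- d on the SD of a single period: dz = 0.66/√(2(1 − 0.2)) = 0.66/√1.6 = 0.522.

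**The plan's own figures.** Paired t-test power is P(|T| > t crit), with T noncentral t on n − 1 df and noncentrality dz√n. At dz = 0.66, n = 16 gives 80.9% at one-sided 0.05 and 69.4% at two-sided 0.05, where 21 are needed. So 16 reproduces as a one-sided figure. At two-sided 0.0167, n = 27 gives 80.1%, so the two-sided Bonferroni assumption fits the planned 27.

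**Reading by the Table 1 pattern.** I simulated three-period crossovers with equal correlation between periods and paired t-tests (100,000 trials, n = 27, two-sided 0.0167). The pattern is INI-PL versus INP-PL significant and INI-OLA versus INP-PL not. The direct contrast is INI-OLA versus INI-PL, significant in the blockade direction.

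| True blockade | Pattern, dz 0.66 | Pattern, dz 0.522 | Direct, dz 0.66 | Direct, dz 0.522 |
|---|---|---|---|---|
| None | 11.6% | 16.7% | 0.8% | 0.8% |
| Half | 59% | 45% | 22% | 13% |
| Full | 79% | 56% | 80% | 57% |

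**Effect of Bonferroni on the predicted null.** With no blockade, INI-OLA versus INP-PL is non-significant in 9% of trials at 0.05 and 20% at 0.0167 (dz 0.66), or 26% and 43% (dz 0.522).

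**Fixed sequence.** Under full blockade, the chance that INI-PL versus INP-PL and INI-OLA versus INI-PL are both significant is 0.68 with each at 0.0167 and 0.85 with each at 0.05 in sequence (dz 0.66), or 0.40 and 0.61 (dz 0.522). With no blockade, the sequence at 0.05 gives a wrong blockade claim in about 2.5% of trials, the usual one-directional error of a two-sided 0.05 test.

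**What 27 completers can say about complete loss.** The protocol gives no margin; I take half the INI effect as an illustration and assume blockade is in truth complete. In SD-of-difference units at dz 0.66 the margin is 0.33. The 95% half-width for INI-OLA versus INP-PL is about 2.056/√27 = 0.396, wider than the margin.
- Equivalence in both directions by two one-sided 0.05 tests (a 90% interval): about 8% power, with about 81 completers needed for 80%. At dz 0.522: under 1%, and about 128.
- The same with a 95% interval: about 1%.
- Only excluding a residual EGP reduction of half the effect, with one limit of the 95% interval: noncentrality 0.33√27 = 1.715 against 2.056, power 38%. At dz 0.522: 26%.

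**The case against.** The strongest reply is that Section 1.2 is a hypotheses section, not a decision rule. The protocol nowhere says that a non-significant INI-OLA versus INP-PL test will be taken as proof. A reader might infer that from Table 1, but the text does not state it. The three comparisons among three treatments must also include INI-OLA versus INI-PL, so the right test can be run. The team's own rat experiment (Figure 3 legend) was read against the insulin-alone group. Ordering of contrasts and success criteria may sit in an SAP that is not shown. All of this stands, and it limits the point to what the protocol itself fixes: the reference group, the predicted null and the three-way Bonferroni.

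Three other strong readings also fail:
- That the direct contrast is unpowered. Under complete blockade it has the same expected size as the powered one, hence 80% at dz 0.66. Power is low only for partial blockade.
- That a smaller or noisier trial is more likely to confirm the hypothesis. The pattern also needs INI-PL to be significant. At n = 8, 16, 27 and 40 (dz 0.66) it appears in about 12%, 17%, 12% and 4% of trials with no blockade, and in 16%, 41%, 59% and 61% with half blockade.
- That the 59% is a false-positive rate. Half blockade is inhibition, a correct positive for Objective 1. Only a claim of complete loss would be too strong.

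The stated 20% attrition might suggest about 22 completers (27 × 0.8 = 21.6). The Participants section replaces dropouts to reach 27 complete sets, so I do not rely on the smaller number.

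**Conclusion.** The point holds as a mismatch between Objective 1 and the way the primary prediction and multiplicity are set out. It does not show that the trial will be misread. If the results were read by the Table 1 pattern, an inert olanzapine would produce it in about 11 to 12% of trials (17% at dz 0.522), against about 1% for the direct contrast at the same alpha. Half blockade would produce it in 59% (45%), where the word 'lost' would not be supported. These figures rest on two-sided 0.0167, 27 completers, equal correlation between periods and the two readings of d. Bonferroni over three pairs is valid, but it costs power that a fixed sequence would recover. It is a cheap and worthwhile improvement, and should be settled before the data are analysed.

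**What to change.** In Section 1.2 and the Data Analysis Plan, name two ordered primary contrasts on EGP: (1) INI-PL versus INP-PL; (2) only if (1) is significant, INI-OLA versus INI-PL. Test each at two-sided 0.05 in fixed sequence, in place of Bonferroni over three pairs. Base the claim that olanzapine inhibits the INI effect on contrast (2).

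Report INI-OLA versus INP-PL as an estimate with a 95% CI, and do not claim complete loss from a non-significant p-value. Claim it only if that interval excludes a residual effect fixed in advance. State whether the exclusion is one-sided or an equivalence test, because that changes the power greatly. With a margin of half the INI effect, 27 completers are unlikely to achieve either.

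The cost is wording only, with no added visits or participants. There are two downsides: no blockade claim is possible if step (1) fails, and the third comparison becomes descriptive. One limit remains. The metabolic arm has no INP-OLA period, so contrast (2) alone cannot separate blockade from a direct olanzapine effect that raises EGP. The report should say so.

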***iv) Preliminary evidence of AP-induced disruptions in central insulin sensing in rodents***

Based on our well established rodent model demonstrating that OLA can acutely induce hepatic insulin resistance, we set out to explore whether this could be occurring via defective insulin sensing at the level of the brain. We used healthy rats (avoiding confounding effects of illness) which were given an acute injection of OLA (to avoid adiposity changes). In our previous work, we had employed hyperinsulinemic euglycemic clamps (HIEC) (15, 38), which we elected to avoid in the present paradigm. The HIEC involves a high dose of intravenously infused insulin which continuously reaches the brain (while glucose levels are kept constant at fasting levels). Thus insulin effects are *not* limited to the brain (and stimulate most tissues in the body), making dissection of peripheral and central effects difficult. Here we used the so called “pancreatic euglycemic clamp procedure” to assess glucose metabolism. During a pancreatic clamp, a peripheral infusion of somatostatin blocks endogenous production of insulin, which is then replaced at “basal” levels *via* a peripheral insulin infusion. Replacement of insulin within physiological “basal” levels allows separate manipulation of central insulin concentrations via an ICV infusion. A central insulin infusion, provided there is no leakage into the circulation, isolates central from peripheral insulin effects. During the pancreatic clamp an exogenous infusion of glucose is adjusted to maintain euglycemia in the animal. The amount of glucose an animal requires to maintain euglycemia (glucose infusion rate), is a measure of whole body insulin sensitivity. A tracer infusion allows for separate determination of glucose production and glucose utilization. Under these conditions, with no evidence of ICV insulin leakage into the periphery, we found that OLA acutely blocked the ability of central insulin to suppress endogenous glucose production by the liver (with *no effect* on glucose disposal), providing, for the first time, evidence that OLA impairs central insulin action, independently of changes in adiposity. Another interesting observation was that there was no effect of OLA on glucose production in the absence of a central insulin stimulus during clamp conditions. (See **Figure 3**, *manuscript in preparation*).

[figure not shown]

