We now have at our disposal a paradigm, employing pancreatic euglycemic clamps in healthy humans demonstrating substantial reductions in endogenous glucose production (mostly a measure of hepatic glucose production), with no changes in glucose disposal, following intranasal insulin administration in healthy males.(31) Intranasal insulin enters the nasal cavity, bypassing the blood-brain barrier, and directly enters the CNS (42), which mimics ICV insulin administration in rodents. Thus, we can propose work, analogous to our rodent model, to examine if OLA can inhibit central (i.e. intranasal) effects of insulin in humans. This also builds on our work establishing that a single dose of OLA in healthy volunteers causes acute perturbations in glucose homeostasis (including elevated fasting glucose levels, likely indicative of OLA-induced increases in endogenous glucose production)(25). Use of young healthy volunteers holds the advantage of: **1)** avoiding confounding illness effects on glucose metabolism; and **2)** represents a population representative of AP-naïve patients who are understood to be most vulnerable to AP-induced metabolic side-effects. Acute dosing of OLA avoiding adiposity change allows us to dissect whether APs can directly inhibit central insulin action in humans.

1. **Research Study Design/Methods**
   1. **Study Duration**

The estimated length of time needed to complete the entire study (from enrolment of the first participant to completion of the last participant) is two years.

- 1. **Study Design and Assessments**

The study will have two separate and parallel arms, conducted in healthy volunteers The first arm will test the metabolic effects of INI and OLA while the second arm will examine the cognitive and neurohemodynamic and neurochemical effects. The metabolic arm will follow a single blind, crossover design wherein all participants will receive each of 3 possible treatments (INP-PL, INI-PL and INI-OLA). The cognitive arm will follow a single-blind, crossover design wherein all participants will receive each of 4 possible treatments (INP-PL, INP-OLA, INI-PL, and INI-OLA). These will be administered at different times in a predetermined sequence to counterbalance the effects of treatments across participants. The assignment of participants to sequences will be at random.

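### The metabolic arm has no INP-OLA treatment, so one prediction in the primary hypothesis is untested and blockade of central insulin rests on an assumption

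*Protocol*

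**What the plan says.** Objective 1 asks whether OLA "can inhibit the ability of a central insulin stimulus (i.e. intranasal insulin administration) to reduce endogenous glucose production (EGP"). Section 1.2 turns this into three EGP predictions. The first is that INI lowers EGP relative to INP. The second is "This effect of glucose production lowering by INI will be lost if OLA is co-administered". The third is "In the absence of INI administration, there will be no difference between OLA and oral placebo (PL").

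Under Study Design and Assessments, the metabolic arm is a crossover in which "all participants will receive each of 3 possible treatments (INP-PL, INI-PL and INI-OLA"). The cognitive arm is the one in which "all participants will receive each of 4 possible treatments (INP-PL, INP-OLA, INI-PL, and INI-OLA"), and it has no clamp and no EGP measurement. Table 1 in section 1.2 has no INP-OLA row, whereas Table 2, for cognition, has one.

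The Data Analysis Plan and Power Calculation section counts three groups and three pairwise comparisons for the metabolic arm. It also refers to four treatment periods there, and for the model addressing the primary hypothesis it says "The four treatments, time, and sequences will be entered as predictors".

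The background bears on OLA without central insulin in two places. For rats, section iv reports that "there was no effect of OLA on glucose production in the absence of a central insulin stimulus during clamp conditions". For healthy volunteers, section vi describes acute effects of a single OLA dose, "including elevated fasting glucose levels, likely indicative of OLA-induced increases in endogenous glucose production".

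**The concern.** The third prediction needs EGP measured on OLA without INI, and no treatment in the metabolic arm supplies it. A statement placed in the primary hypothesis therefore has no data to test it.

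The gap reaches the main conclusion. Inhibiting the ability of INI to lower EGP means that the INI effect differs with and without OLA, which is an interaction. The arm measures the INI effect only under oral placebo. If EGP at the INI-OLA visit is back at the INP-PL level, either OLA has blocked intranasal insulin, or intranasal insulin has worked as usual and OLA has raised EGP by a separate route. Either would match the INI-OLA row of Table 1.

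**Working it through.** **Inputs.** The three treatments come from Study Design and Assessments. The 20% INI effect, d = 0.66, correlation 0.2 and n = 27 come from the Data Analysis Plan and Power Calculation section. Sampling and dose times come from the clamp description.

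**1. What the three visits can estimate.** Write mean EGP as μ for INP-PL, with INI effect I, OLA effect O and interaction X:

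- INP-PL = μ
- INI-PL = μ + I
- INI-OLA = μ + I + O + X
- INP-OLA = μ + O (not observed)

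Three means carry four parameters, so the design matrix has rank 3. The estimable contrasts are INI-PL − INP-PL = I, INI-OLA − INI-PL = O + X, and INI-OLA − INP-PL = I + O + X. O and X appear only as a sum. With INP-OLA added the rank would be 4 and both would be estimable.

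**2. Size, using the protocol's 20% effect.** Set INP-PL = 100 and I = −20. If the observed means are 100, 80 and 100, then O + X = 20 and X = 20 − O:

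| Assumed O | Unobserved INP-OLA | Implied X | Share of INI effect blocked, X/20 |
|---|---|---|---|
| 0 | 100 | 20 | 100% |
| 10 | 110 | 10 | 50% |
| 20 | 120 | 0 | 0% |

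Likewise, means of 100, 80 and 90 look like half blockade but also follow from O = 10 with no blockade. The table is on the additive scale. The result does not depend on n.

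**3. The count of treatments.** Table 1, the design section, the three study occasions and the three pairwise comparisons all give three. The references to four periods and four treatments fit only the cognitive arm.

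**4. What the pre-INI data could add.** The tracer runs throughout the clamp and blood is drawn every 30 minutes from t = −120 to 0, after the day 0 and day 1 OLA doses. EGP before INI at the INI-OLA visit can be compared with the mean of the two oral-placebo visits. Its variance is σ²(1 − 0.2)(1 + 1/2) = 1.2σ², so SE = σ√(1.2/27) = 0.21σ.

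σ depends on how d = 0.66 is read. The stated 16 subjects is reproduced by a paired t-test with d on the paired difference and one-sided alpha 0.05 (power 0.809); two-sided 0.05 gives 21. With d on the between-subject SD and correlation 0.2, the results are 25 and 31. Both readings are therefore shown:

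- d on the between-subject SD: σ = 20/0.66 = 30.3 points. The 95% half-width is 2.06 × 0.21 × 30.3, about 13 points.
- d on the paired difference: σ = 30.3/√1.6 = 24 points. The half-width is 2.06 × 0.21 × 24, about 10.4 points.

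An estimate near zero would exclude a 20-point rise from the earlier doses, but not a 10-point rise. This assumes 27 complete subjects, the same SD and correlation before INI as in the power calculation, and tracer steady state.

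The window also closes as the day-2 OLA dose is given at t = 0. The stated peak at 4 to 6 hours is t = 240 to 360 minutes, the last third of the post-INI period. The contrast cannot see that dose. Expressing EGP after INI relative to each visit's own pre-INI value does not help, because that change still mixes the day-2 dose with INI.

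**The case against.** The three-treatment design is consistent where it matters and looks deliberate. Table 1, the design text and the comparison count agree, all three pairwise contrasts are estimable within subject, and sparing volunteers a fourth eight-hour clamp is a reasonable trade-off in a proof-of-concept study. That stands, and a fourth visit is not asked for.

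The third prediction also has a stated basis. The rat experiment examined OLA without central insulin under a pancreatic clamp, and the human clamp likewise suppresses and replaces insulin, glucagon and growth hormone. The human evidence the other way infers EGP from fasting glucose and is not described as clamp data. A reader might conclude that the protocol itself shows that OLA alone raises EGP. It does not: its evidence is mixed. But the support for no effect comes from another species, and section 1.2 presents it as part of the primary hypothesis, not as an assumption.

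A reader might also take the count of four as a defect in the primary model. The same section says three groups, and a model cannot fit a level without data. It is an editorial slip that biases nothing.

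Leaving the matter to a statistical analysis plan does not resolve it. Treatments and hypotheses are fixed in the protocol, and no analysis recovers a missing cell.

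**Conclusion.** The point holds. From the three visit means, neither the prediction for OLA without INI nor the INI x OLA interaction can be estimated. An INI-OLA mean equal to INP-PL is compatible with anything from 100% to 0% blockade as the unobserved effect of OLA alone runs from 0 to 20% of INP-PL EGP. The primary contrasts directly support the statement that EGP under INI is higher with OLA than with PL. Blockade of central insulin follows only if OLA has no effect on EGP without INI.

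Two stronger readings are not supported. One is that the trial's data cannot discriminate at all: that is true of the visit means, but pre-INI EGP gives a partial check on the day 0 and day 1 doses. The other is that a purely additive effect will be reported as central insulin resistance: the protocol fixes no reporting wording, so this is a risk of interpretation and not a stated plan.

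**What to change.** 1. In section 1.2, mark the prediction about OLA without INI as an untested assumption resting on the rat clamp data, or remove it from the primary hypothesis.
2. In the Data Analysis Plan and Power Calculation section, change four treatments and four treatment periods to three for the metabolic arm.
3. State that the primary contrasts support the conclusion that EGP under INI is higher with OLA than with PL, and that blockade of central insulin action is conditional on the assumption in item 1.
4. Optionally, add the contrast of pre-INI EGP between the INI-OLA visit and the two oral-placebo visits as a supportive check of the day 0 and day 1 doses only. It cannot show the absence of a direct effect of the day-2 dose, and a clean result must not license the full blockade claim.

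The cost is wording, at most one extra contrast on samples already planned, and a weaker conclusion.
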